#### 2.3.3. Data Collection

At baseline, sociodemographic and clinical variables will be collected to characterize the sample and explore potential factors associated with response to the intervention. These variables will include age, sex, place of residence, educational level, employment status, family structure, need for a caregiver, caregiver role, pain characteristics, pain duration, pain location, previous pharmacological treatment, previous use of NPhTs, and beliefs about their benefits. Collecting these variables will allow the sample to be described and the results to be contextualized from clinical, social, and gender perspectives.

For the quantitative assessment, the study questionnaires, scales, and surveys completed by the participants will be used. These questionnaires will be embedded in the MoviSalud mobile app, allowing all questionnaires (baseline and follow-up) to be completed and recorded by both groups (control and intervention). Once the participants are enrolled in the study (prior to randomization), they will receive a message explaining how to download the app and access it to enter their baseline data, and they will be provided with a username and password. The participants will be offered telephone support to resolve any questions or technical issues. If a patient has difficulty using the application, they will be asked whether a family member can assist them, in which case support will be provided through that family member. If no such support is available, individualized assistance will be offered either by telephone or in person at the hospital, with an appointment arranged as needed. Reminders will be sent regarding the assessments to be completed at each follow-up time point, and the application will enable communication between patients and healthcare professionals to resolve questions and issues.

For the qualitative assessment, in-depth semi-structured interviews will be conducted following an interview guide developed for this study. The interviews will be audio-recorded and subsequently transcribed for analysis. They will be conducted by nurses with experience in qualitative methodology, care provision, and CP management. These researchers will not be involved in delivering the workshop, to help participants express their experiences, views, and perceptions of the intervention freely. The semi-structured interview guide is included as Appendix B.

The research team will be able to use the MoviSalud professional portal to monitor completion of the planned questionnaires and records. They will also be able to resolve incidents related to use of the app during the data collection process.

#### 2.3.4. Data Management

The study data will be managed using the MoviSalud RPM (Remote Patient Monitoring) platform, adapted for this project. The platform will centralize data entered by the participants through the mobile app and will allow the research team to access these data through a professional web portal.

An internal medicine physician from the research team will conduct recruitment through a telephone interview to verify whether the patient meets the inclusion criteria. If eligible, the physician will inform the patient about this study and the possibility of being allocated to either the intervention or the control group and will obtain informed consent. Once a cohort of 40 patients has been recruited, the physician will notify the research support technician, who will register and enroll them in the app.

Once enrolled in the platform, the patient will have access exclusively to the baseline assessment forms prior to randomization. Once patients have completed the baseline assessment, randomization will be requested. Treatment allocation cannot be predicted in advance.

Allocation to the study arm will be performed automatically by the system through an atomic and irreversible transaction, with a timestamp and audit trail; no individual will be involved in the allocation process. The recruitment wave will then be closed, the corresponding workshop cohort will be established, and the control group will be activated. Within each combination of recruitment wave and stratum, permuted blocks of size 4 or 6 will be generated, with the block size selected randomly and independently for each block, with a probability of 0.50 for each size. With recruitment waves of approximately 40 participants divided into two sex strata, and considering the higher expected prevalence of women among individuals with chronic pain, the male stratum may comprise approximately 10–12 participants per wave. Blocks of size 8 would, therefore, result in a relatively high number of incomplete blocks at the end of each recruitment wave, which would be contrary to the intended purpose of blocking. Block sizes of 4 and 6 limit the maximum imbalance within each stratum to three participants, while preserving allocation unpredictability.

The allocation sequence will be generated using the PCG64 pseudorandom number generator [41], as implemented in the randomization module of the MoviSalud platform (version 3.21.5; Socioemprende S.L., Valencia, Spain), initialized with a cryptographically secure seed. The seed will be encrypted and securely stored, and its SHA-256 hash will be timestamped before the first allocation is issued by the module. This will allow the sequence to be reproduced and verified for audit purposes without making it possible to anticipate future allocations at any time. Independent verification will assess the actual allocation ratio, block lengths, integrity of stratification, uniformity, and absence of serial patterns. The entire process will be documented in a record signed by both responsible individuals. To ensure that methodological decision-making and technical implementation are not assigned to the same individual, these functions will be separated. A methodological lead will define and approve the parameters of the allocation scheme, independently verify the generated sequence before its implementation, and sign the sequence-generation record. A technical lead will configure the module according to the approved specifications, execute sequence generation, safeguard the seed, and ensure technical segregation and traceability. The technical lead will not determine the methodological parameters but will implement those previously approved. Neither individual will participate in patient referral, screening, delivery of the workshop, or outcome assessment.

The platform will support the creation of users, profiles, and differentiated permissions. It will also allow anonymized case management and separate environments for participants in the intervention and control groups. The data will be hosted in a secure cloud environment provided by Amazon Web Services, in accordance with Spanish and European data protection and security regulations. MoviSalud includes authentication mechanisms, access control, secure communication, and protection against unauthorized access.

The study data will be exportable in CSV files for the research team. Once data collection has been completed, the quantitative database will be cleaned in a spreadsheet and then imported for statistical analysis. For the qualitative strand, interviews will be transcribed and checked before data management and analysis.

### 2.4. Ethical Considerations

This study was approved by the Research Ethics Committee of Hospitales Universitarios Virgen Macarena y Virgen del Rocío in October 2025 (SICEIA-2025-002927). The trial is registered at ClinicalTrials.gov under the identifier NCT06440668. Any substantial protocol amendments will be reported to the relevant ethics committee and, where applicable, to the trial registry, in accordance with applicable ethical and regulatory procedures.

All of the participants will receive oral and written information about the study aims, planned procedures, random allocation to study groups, data collection and processing, and the potential benefits and burdens of participation. Participation will be voluntary and will require written informed consent before inclusion in the study. The participants may decline to participate or withdraw from this study at any time by informing the workshop coordinator, without this affecting their usual healthcare.

Personal and clinical data will be treated confidentially and coded to preserve the participants’ identities. Access to information will be restricted to the authorized research team. The results will be analyzed and disseminated in aggregate and anonymized form.

As this study includes a qualitative strand, the participants involved in the qualitative strand will provide additional written informed consent for the semi-structured interviews and for audio recording. The recordings will be transcribed and analyzed while preserving the participants’ confidentiality and anonymity.

The intervention under evaluation is non-pharmacological and is considered low risk. However, participation may involve time burden, questionnaire completion, and possible emotional discomfort when reflecting on the experience of CP. The participants allocated to the control group will be offered the workshop after completion of the comparative follow-up period, to ensure that they are not denied the opportunity to receive a potentially beneficial intervention.

The psychologist on the research team will be available in specific cases in which a patient requires urgent psychological support during the workshop or during the qualitative study interview. After completion of the workshop and/or interview, if the research team considers that a patient would benefit from psychological support, the patient will be advised to seek such support after completing the study.

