#### 2.1.3. Intervention

The participants allocated to the intervention group will receive a multicomponent psychoeducational workshop focused on self-management, pain control, and emotional regulation, based on NPhTs.

The participants will continue to receive their usual healthcare. Participation in the workshop will not require discontinuation or mandatory modification of analgesic medication, psychotropic drugs, or any other usual treatments. Any reduction, withdrawal, or modification of pharmacological treatment will occur, where applicable, at the patient’s decision and/or according to the judgement of the healthcare professionals responsible for their usual clinical care. Current pharmacological treatment will be recorded both at baseline and at the different follow-up time points (months 1, 4, and 7, with the latter only in the intervention group), as well as whether the participants are receiving physiotherapy, psychological treatment, or complementary therapies (specifying which ones); whether they engage in regular physical exercise (specifying the type and frequency); whether they are currently receiving care from a pain management unit; and whether they use healthcare services due to pain (emergency department visits, scheduled outpatient visits, and hospitalizations). This information will allow us to document changes in the healthcare received over the course of this study.

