All of the participants will have access to specific MoviSalud mobile app (version 3.21.5; Socioemprende S.L., Valencia, Spain), features to complete questionnaires (baseline and follow-up) in both groups (control and intervention). The MoviSalud platform currently supports the management of a range of clinical conditions across specialties such as Cardiology, Internal Medicine, and Pulmonology, among others, and is available for use in both public and private hospitals following its purchase. This platform was selected because of its previous experience in hospital settings and the high level of satisfaction reported by healthcare professionals who have used it. It will be used primarily for data collection. Only in the intervention group will it also be used to support follow-up, as selected materials (audio recordings of the main meditation exercises, exercise guides, and an explanatory video on chronic pain) will be uploaded to the application. These materials will serve as reminders and reinforcement to help patients continue applying the tools practiced during the workshop. These materials will become available upon completion of the workshop and will remain accessible until the end of the follow-up period (month 7). Only the participants in the intervention group will have access to these intervention-related digital contents.

During the first session, a messaging group will be created for each workshop and coordinated by a volunteer patient. The group will be used to share reinforcement materials from the sessions, channel questions to the workshop director, and communicate attendance-related incidents. It will also provide a space for peer support, helping to strengthen group cohesion and a sense of belonging during the intervention.

The final session will include workshop closure, a review of the tools learned, and participants’ final assessment of the workshop. The participants will also receive a guide reinforcing the content covered during the workshop. Access to the MoviSalud mobile app will be maintained so that the participants can continue applying the tools and recommendations after the workshop and complete the follow-up assessments.

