### 2.3. Data

#### 2.3.1. Outcomes

The primary outcome will be the between-group difference in health-related quality of life (QoL), assessed using the EuroQol-5D (EQ-5D) index score [27] at one month, adjusted for baseline values, and reported with its 95% confidence interval. Intervention effectiveness will be evaluated primarily on the basis of this randomized between-group comparison. Improvements greater than 0.10 in the EQ-5D index will be used to aid interpretation of the magnitude of the estimated treatment effect and will not constitute a separate criterion for declaring effectiveness.

The EQ-5D index will also be assessed at 4 months in both randomized groups as a supportive secondary assessment. The additional month-seven assessment in the intervention group will be considered an exploratory evaluation of the maintenance of effect and will not be used for randomized between-group inference because the control group will be offered the workshop after the 4-month comparative period.

Secondary outcomes will include pain intensity, pain catastrophizing, subjective well-being, self-esteem, mood, resilience, anxiety and depression, medication use, health habit improvement, and healthcare resource use. The participant experience-related outcomes will include satisfaction, perceived usefulness of the techniques learned, recommendation of the workshop, perceived impact on daily life, and suggestions for improvement.

The planned outcomes and measurement instruments are summarized in Table 1. The use of validated scales and ad hoc patient-reported outcome and experience measures in previous evaluations of the workshop is described elsewhere [22,23].

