The participants who do not complete the 4-month questionnaires will be considered lost to follow-up. Their sociodemographic and clinical characteristics, as well as their baseline scale scores (included in the baseline assessment), will be analyzed to characterize the profile of these patients. If, during follow-up, a participant from either the control or intervention group modifies their medication or the therapies they receive, they will not be considered lost to follow-up; they will remain in this study, and changes will be assessed at 1, 4, and 7 months. The patients originally assigned to the control group will not be included as part of the intervention group in this study. Although they will be offered the opportunity to participate in a workshop after completing their follow-up as controls, they will not be considered part of the intervention group for study purposes.

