**Session 5:**
**Objectives:** To review the homework assignments and provide guidance when necessary; to review the tools, advice, and therapies presented and practiced during the workshop; to address questions about the tools; to collect the tracking sheets completed at home; to evaluate outcomes using scales and questionnaires through the app; and to thank patients for their participation and work. **Content, techniques, facilitator, duration, and materials:** 1. Sharing the results of homework assignments. (Physician 1) 15 min. 2. Presentation and discussion: Review of the tools explained during the workshop. Group sharing. Question-and-answer session. (Physician 1) 60 min. 3. Collection of the tracking sheets completed by patients during the workshop and provision of the recommendations guide. (Physician 1) 15 min. 4. Talk: Experience shared by a patient from a previous workshop. (patient contributor) 20 min. 5. Activity: Workshop evaluation and completion of assessment scales. (patients, with guidance from facilitators) 40 min. 6. Activity: Physical exercise through dancing. (T: EP) (Physiotherapist) 20 min. 7. Talk: Information about the upcoming follow-up dates. (Physician 1) 10 min. 8. Activities: Thanking patients for their trust in the workshop and encouraging them to continue applying and further developing the tools to control pain and cope better with illness; final closing and farewell. (Physician 1) 30 min. 9. Materials provided: Guide containing the tools presented during the workshop and additional advice; information on chronic pain patient associations located in the hospital’s catchment area.

T: Technique used; ED: pain education; TCC: cognitive behavioral therapy; TAC: Acceptance and Commitment Therapy; PRT: Pain Reprocessing Therapy; TAE: exercises to identify and improve low self-esteem; Ho’oponopono: technique for working on forgiveness; MC: motivation for change; EHS: healthy lifestyle education; EP: physical exercise. Note: PowerPoint presentations containing the content of the talks are available. Each facilitator developed their own presentations, which will remain unchanged throughout this study to ensure intervention fidelity. In some sessions, printed supporting materials are also provided to patients, as indicated in the table at the end of each session.

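### Patients thought likely to benefit from psychological support are advised to seek it only after the study, most naturally month 7 in the workshop arm; deleting or clarifying one clause fixes this

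*Protocol article*

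**What the plan says.** Section 2.4 makes two provisions for psychological support. The first is for urgent need: the team's psychologist is available when a patient "requires urgent psychological support during the workshop or during the qualitative study interview". The second is for need recognised afterwards. If the team considers, once the workshop and/or interview is over, that a patient would benefit from support, "the patient will be advised to seek such support after completing the study".

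Other parts of the article bear on how this works:

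- Section 2.1.3 (Intervention) continues usual care. At baseline and each follow-up it records "whether the participants are receiving physiotherapy, psychological treatment, or complementary therapies". It also identifies month 7 as the end of follow-up, the point to which the app materials stay available.
- Section 2.3.3 (Data Collection) says that "the application will enable communication between patients and healthcare professionals to resolve questions and issues".
- Section 2.5.1 (Quantitative Analysis) says of participants who change medication or therapies that "they will remain in this study, and changes will be assessed at 1, 4, and 7 months".
- Section 2.3.1 (Outcomes) says that the month-7 assessment "will not be used for randomized between-group inference".
- Appendix A, Table A1, Session 5 includes "Workshop evaluation and completion of assessment scales. (patients, with guidance from facilitators) 40 min".

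**The concern.** The sentence on non-urgent need tells a patient in whom the team already sees a likely benefit to wait. Section 2.4 itself expects that reflecting on pain may cause emotional discomfort. The psychologist's cover described there is limited to urgent need during the workshop or interview. For need recognised later, this sentence is the section's only provision.

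Nothing in the confirmatory analysis calls for the wait. Psychological treatment during the study is permitted and recorded, and a patient who starts it stays in the trial. What is at stake is a delay in care for some workshop-arm patients, not the validity of the primary result.

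**Working it through.** The plan gives no figure to reproduce here. The check is a reading of the text followed by timeline arithmetic.

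**Inputs**

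- Workshop end and first follow-up: month 1 (section 2.3.2, Table 2).
- Interviews: preferably 1 to 2 months after the intervention, that is months 2 to 3 (section 2.3.2, Table 2).
- Last assessment in both randomized groups: month 4 (section 2.3.2, Table 2).
- End of follow-up in the workshop arm: month 7 (sections 2.1.3 and 2.3.2, Table 2).

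**Which completion is meant.** The sentence opens by placing the judgement after the workshop and/or interview. If its closing phrase meant the same moment, it would add nothing. Read as adding something, it points to a later time, and the end of follow-up in the workshop arm is month 7.

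**Wait = month of study completion minus month when the benefit is recognised**

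| Reading | From workshop end | From interview |
|---|---|---|
| End of follow-up, month 7 | 7 − 1 = 6 months | 7 − 3 = 4 to 7 − 2 = 5 months |
| Patient's own interview, month 2 to 3 | 2 − 1 = 1 to 3 − 1 = 2 months | 0 |

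**Splitting the month-7 wait at the last randomized comparison**

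- Up to month 4: 4 − 1 = 3 months from workshop end; 4 − 3 = 1 to 4 − 2 = 2 months from interview.
- After month 4: 7 − 4 = 3 months in every case. That is 3/6 = 50% of the wait from workshop end, and 3/5 = 60% to 3/4 = 75% of the wait from interview.

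**Does any analysis need the deferral?**

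- *Month 1, confirmatory.* Workshop patients are scheduled to complete their scales in session 5. The advice comes after the workshop, so removing the deferral does not change this endpoint.
- *Month 4, supportive.* The prompt would reach only the workshop arm, because section 2.1.3 limits controls' study contact to the research support technician. Keeping this contrast free of a one-sided prompt is a conceivable reason for waiting, but the article does not state it.
- *Month 7, exploratory.* This assessment has no control group and is excluded from randomized inference. Protecting a randomized contrast therefore cannot justify the stretch from month 4 to month 7.

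**The case against.** The strongest reply is that the phrase is ambiguous. The sentence before it mentions the qualitative study interview, so the study could mean that component only, and the wait would then be short or nil. The phrase might also describe when the advice is given. This stands as a reason to clarify. It does not make the wording safe, because staff can reasonably read it as month 7. If it dates the advice itself, the patient is not even prompted until then.

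Second, nothing restricts care. Usual care continues, psychological treatment is not prohibited, patients can reach professionals through the app and may withdraw freely, and urgent need during the workshop or interview is covered. This also stands. It makes 6 months an upper figure that applies only to a patient who follows the advice literally, and it keeps the point minor.

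Third, an article condenses a fuller protocol, and referral procedures may be set out there. That would answer a complaint about missing detail. Here the article states a rule, and the rule is what needs changing.

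Fourth, immediate advice could bring extra psychological care into one arm before the 4-month contrast. This is a real, small cost. It supports a deferral to month 4 at most.

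**Conclusion.** The concern holds as a minor point of participant welfare. On the natural reading, a workshop-arm patient who follows the advice literally waits up to about 6 months from workshop end, or 4 to 5 months from interview, and the last 3 months come after the final randomized comparison. On the narrower reading, the wait is 1 to 2 months from workshop end and none from interview.

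These figures assume that the benefit is recognised at workshop end or at interview and that the scheduled timings are kept. The article does not say how many patients are affected. The 1-month primary result, the sample size and the significance level are unaffected. Confidence is medium, because the size depends on what completing the study means.

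**What to change.** Delete the final four words of the sentence in section 2.4, so that patients are advised to seek support through usual care when the benefit is recognised. If only completion of the qualitative part is meant, say so. If the sponsor wants to keep the 4-month contrast free of the prompt, state that reason and end the deferral at month 4.

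Report psychological treatment started during follow-up by arm at months 1 and 4, and for the intervention arm at month 7. The records planned in section 2.1.3 already supply this.

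The cost is one clause, plus the participant information if it repeats the clause. No new form, contact with controls or change in sample size is needed. The downside is that some extra psychological care may enter the workshop arm before the supportive 4-month contrast and the exploratory month-7 assessment; this should be noted when they are interpreted. Ending the deferral at month 4 removes that downside for the 4-month contrast.
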